**Methods:**

The cross-sectional study includes a multifactorial mixed-measure design. Between-subject factor grouping the sample will be Parkinson’s Disease (early PD vs. healthy). The within-subject factors will be the task complexity (single- vs. dual-task) in each motor activity, i.e., overground walking, semi-tandem stance, and isometric knee extension, and a walking condition (wide vs. narrow lane) will be implemented for the overground walking activity only. To study dual-task (DT) effects, in each motor activity participants will be given a secondary cognitive task, i.e., a visual discrimination task for the overground walking, an attention task for the semi-tandem, and mental arithmetic for the isometric extension. Analyses of DT effects and underlying neuronal correlates will focus on both gait and cognitive performance where applicable. Based on an a priori sample size calculation, a total N = 42 older adults (55–75 years) will be recruited. Disease-specific changes such as laterality in motor unit behavior and cortical control of movement will be studied with high-density surface electromyography and electroencephalography during static and dynamic motor activities, together with whole-body kinematics.

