*Managing adverse effect*.** The protocol and proposed experiments were modified after the pilot trials to minimize the occurrence of factors that led to experiment termination. Specifically, the number of stimuli and the duration of conditions were kept low enough to avoid fatigue but high enough to ensure adequate data quality, while the breaks between tasks/conditions were made sufficiently long. If reasons such as fatigue will nevertheless lead to a request for an interruption, the investigation will be terminated. Similarly, if participants will experience dizziness or will experience adverse effects for other reasons, the examination will be terminated. A physician will be present to ensure physical safety. The experimental day is organized in three experiments, so the recorded data will provide valuable insights despite the number of experiments completed.

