### Statistical analysis and power calculation

Descriptive data will be presented as means (M) and standard deviations (SD). The homogeneity of variances and normality of distribution of parameters will be tested with Levene's test and Shapiro-Wilk test, respectively. Using univariate analyses of variances (ANOVA), the between-subject factor grouping the sample will be
*PD* (early PD vs. no PD), while the within-subject factors will be the
*task complexity* (ST vs. DT) in each motor activity, i.e., the overground walking, semi-tandem stance, and isometric force knee extension, as well as the
*walking condition* (wide vs. narrow) for the overground walking only. Significance will be set at alpha = 0.05. The effect size will be presented as the unbiased adjusted partial eta squared
^
78
^. All post-hoc comparisons will control for multiple comparisons (e.g., Bonferroni). Statistical analyses will be done using SPSS (IBM, SPSS Inc, Chicago, IL, United States) or R (R Core Team, 2013).

Sample size estimation calculated using g*Power software (a priori: F-tests; ANOVA: repeated measures, within-between interaction; effect size f = 0.2; alpha error probability = 0.05; power (1-beta error probability) = 0.8; number of groups = 2; number of measurements = 3) revealed a total of
*N* = 42 subjects, half of who will be healthy older adults, and the other half will encompass people with early-stage PD.

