We anticipate several challenges in conducting this study. First, recruitment of people in the early-stage of PD will be a relatively lengthy process because of the limited number of such people in the Trieste region (Italy). Second, the complexity of the test blocks is planned in such a way that subjects will have enough breaks and will be able to rest between trials. However, the long protocol (about 5 hours) will require careful preparation and handling with constant medical monitoring. We will try to maintain motivation throughout the measurement and avoid fatigue by taking multiple breaks. Finally, in our sample of early PD, we do not expect the occurrence of FOG during our measurements. A hypothetical explanation for the occurrence of FOG is that the narrowness of the corridor causes an increase in optic flow, as the visual image of near objects moves faster on the retina than that of more distant objects
^
79
^. Thus, visual and vestibular signals provide conflicting information to the brain in such situations. In our case, participants will be walking in a wide and narrow lane that gives the impression of a narrower path but does not enforce the narrow space/corridor.

In summary, the current study employs a state-of-the-art methodology to assess neuromuscular outcomes that aim to elucidate important underlying mechanisms of neural control of movement during dual motor-cognitive tasks in healthy older adults and in people with early-diagnosed PD. Thus, we aim to uncover an early biomarker of movement (in)efficiency.

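### The stated power of 0.8 at N = 42 is computed for three repeated measurements, not for the two-level single- versus dual-task test described, and it carries no allowance for terminated sessions

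*Protocol article*

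**What the plan says.** Under Statistical analysis and power calculation, the protocol article reports an a priori G*Power run of the type "ANOVA: repeated measures, within-between interaction", with "effect size f = 0.2", "alpha error probability = 0.05", "power (1-beta error probability) = 0.8", "number of groups = 2" and three measurements. The result is 42 participants, half with early Parkinson's disease (PD) and half healthy. Neither the correlation among repeated measures nor the non-sphericity correction is given.

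The same section, and Trial design, define task complexity as single task against dual task. That makes a 2 x 2 design for stance and for isometric extension, and a 2 x 2 x 2 design for walking, where lane width is a second two-level factor.

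The abstract turns the calculated number into the recruitment number: "Based on an a priori sample size calculation, a total N = 42 older adults (55–75 years) will be recruited". Under Managing adverse effect, a fatigue-related request to interrupt ends the investigation, and "if participants will experience dizziness or will experience adverse effects for other reasons, the examination will be terminated". The Discussion lists session length among the challenges: "the long protocol (about 5 hours) will require careful preparation and handling with constant medical monitoring". Under Procedure, tasks, and stimuli, the order of activities is the same for everyone: walking, then stance, then isometric extension.

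**The concern.** There are two separate gaps between the stated power and the analysis.

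The first is the number of measurements. A within-between interaction with three measurements has two numerator degrees of freedom and draws on three observations per person. Group x task complexity with two levels has one numerator degree of freedom and two observations per person. At the same f and rho these tests have different power. No within-subject factor in the analysis section has three levels. The three motor activities cannot supply one, because Trial design says that their dual-task conditions cannot be compared directly.

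The second is that 42 is both the calculated minimum for analysis and the number to be enrolled, in a design that has a rule for ending sessions.

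At stake is how null results are read. Higher dual-task costs in PD are hypothesised for all three activities. A non-significant interaction, above all in stance or isometric extension, would be judged against 80% power that those analyses may not have.

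**Working it through.** **Inputs.** From the power section: f = 0.2, alpha = 0.05, k = 2 groups, m = 3 measurements, target power 0.8, N = 42. From Trial design: m = 2 for task complexity. Not stated, so assumed: rho and epsilon.

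**Formula** (G*Power within-between interaction, noncentral F):
- lambda = f² x N x m x epsilon / (1 − rho)
- df1 = (k − 1)(m − 1) x epsilon
- df2 = (N − k)(m − 1) x epsilon
- power = P(F' > F critical), where F' is noncentral F with parameter lambda

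**Step 1: reproduce the plan's figure.** Take m = 3, rho = 0.5, epsilon = 1. Then lambda = 0.04 x 42 x 3 / 0.5 = 10.08, df = 2 and 80, and power = 0.803. The smallest even N that reaches 0.80 is 42, so the stated N is reproduced. With epsilon held at 1, rho = 0.4 would need 50 and rho = 0.6 would need 34.

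**Step 2: the test described.** Take m = 2, rho = 0.5. Then lambda = 0.04 x 42 x 2 / 0.5 = 6.72, df = 1 and 40, and power = 0.716. Epsilon has no role with two levels. Reaching 0.80 would take N = 52.

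**Step 3: sensitivity to rho.** Take m = 2, rho = 0.6. Then lambda = 0.04 x 42 x 2 / 0.4 = 8.40, df = 1 and 40, and power = 0.807. Rho 0.6 does not give N = 42 with three measurements if epsilon is 1. It does if epsilon is about 0.75: lambda = 0.04 x 42 x 3 x 0.75 / 0.4 = 9.45, df = 1.5 and 60, power = 0.810, and 42 is again the smallest even N. So rho 0.5 with epsilon 1 is not the only pair that fits the stated N.

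**Step 4: loss of evaluable participants** (rho = 0.5, epsilon = 1; the numbers lost are assumptions):

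| Evaluable N | m = 3 (as calculated) | m = 2 (as tested) |
|---|---|---|
| 42 | 0.803 | 0.716 |
| 41 | 0.793 | 0.705 |
| 40 | 0.782 | 0.693 |
| 38 | 0.758 | 0.670 |
| 36 | 0.733 | 0.645 |

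On the plan's own settings, one lost participant takes power just below 0.80, two cost about 2 points, and six cost about 7. Changing from three measurements to two costs 0.803 − 0.716 = 0.087, about 9 points, with nobody lost. That exceeds the cost of losing six.

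**The case against.** The strongest reply is that no arithmetic is wrong. The 0.8 is an input to a design calculation that reproduces exactly; it is a target, not a promise about the analysed sample. That stands for the G*Power run itself. It does not answer the mismatch, because the run is for a test with a different number of measurements from the one the same section sets out.

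A second reply is that an article may leave drop-out rates and replacement rules to the full protocol. That is fair. The absence of a rate is not the point here, and a replacement rule elsewhere could remove the attrition part altogether.

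Third, a reader might infer that the study is bound to miss its power because sessions will be lost. The documents do not support that:
- No termination rate is given.
- Stimuli, durations and breaks were adjusted after piloting to limit terminations.
- Eligibility is checked on the first measurement day, before the experimental day.
- Data from completed activities are kept.
- Walking, the core activity, comes first.

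One or two losses cost 1 to 2 points. What remains is that 42 has almost no slack on the settings that most simply reproduce it, and that any loss would fall mainly on the two later activities.

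Fourth, rho is unknown, and its effect is larger than that of modest attrition. This is correct, and it limits how firmly 0.72 can be stated.

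**Conclusion.** The point holds in this form. The stated 0.8 belongs to a three-measurement interaction, whereas the plan tests task complexity at two levels. With f = 0.2 and rho = 0.5, power for that test is about 0.72 at 42 complete participants. If rho were 0.6 it would be about 0.81, so a shortfall is likely on the simplest reading of the inputs but not proven. The 0.72 fits stance and isometric extension most directly; in walking each task level is seen in two lanes, which the two-measurement formula does not model.

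Attrition is the smaller and conditional part. At rho 0.5, with 36 to 40 evaluable (an assumption), power would be about 0.65 to 0.69 for two levels, or 0.73 to 0.78 on the plan's three measurements.

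**What to change.** Keep N = 42 and say that it is the number recruited. State the rho and epsilon entered in G*Power. Restate the power for the two-level Group x task complexity interaction at 42. Then give it for each activity over a plausible evaluable range, for example 36 to 40, labelled as an assumption. If the three measurements referred to a specific three-level comparison, name that comparison and say that the 0.8 applies to it alone.

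The cost is a stated figure that will probably be less favourable. No extra participants are needed, which matters because the Discussion expects recruitment of people with early PD to be slow.

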## Discussion

Recent advances in neuroimaging, wearables and wireless technologies offer a range of opportunities to better understand human behavior and link it to cortical and muscular activation patterns. MoBI enables the investigation of brain and muscle dynamics in conjunction with biomechanical parameters and secondary sensorimotor processes. The lack of scientific evidence in clinical populations has prompted us to conduct the present study with people with early-diagnosed PD. Therefore, the aim of this study is to investigate the differences in functional static and dynamic performance between healthy and age-matched early-PD populations. The effect of interest will be investigated through DT effects and associated neuromuscular underpinnings. Specifically, using the MoBI approach, EEG, HD-EMG, and whole-body kinematics will be recorded under various ST and DT conditions to uncover the underlying mechanisms of force production, balance, and gait control in people with early-diagnosed PD. The underlying processes of interaction between motor and cognitive tasks will be identified at behavioral and neurophysiological levels under conditions of varying complexity. The general hypothesis is that there are performance differences and corresponding neuromuscular correlates between subgroups, with the highest neuromuscular compensations occurring in the PD group. We hypothesize that the performance differences are related to the different motor-cognitive processes such as stimulus input, resource allocation, and movement execution. Our goal is to find a neuromuscular biomarker that distinguishes the two populations and thus reflects an early onset of neuromuscular deficit in PD.

We anticipate several challenges in conducting this study. First, recruitment of people in the early-stage of PD will be a relatively lengthy process because of the limited number of such people in the Trieste region (Italy). Second, the complexity of the test blocks is planned in such a way that subjects will have enough breaks and will be able to rest between trials. However, the long protocol (about 5 hours) will require careful preparation and handling with constant medical monitoring. We will try to maintain motivation throughout the measurement and avoid fatigue by taking multiple breaks. Finally, in our sample of early PD, we do not expect the occurrence of FOG during our measurements. A hypothetical explanation for the occurrence of FOG is that the narrowness of the corridor causes an increase in optic flow, as the visual image of near objects moves faster on the retina than that of more distant objects
^
79
^. Thus, visual and vestibular signals provide conflicting information to the brain in such situations. In our case, participants will be walking in a wide and narrow lane that gives the impression of a narrower path but does not enforce the narrow space/corridor.

In summary, the current study employs a state-of-the-art methodology to assess neuromuscular outcomes that aim to elucidate important underlying mechanisms of neural control of movement during dual motor-cognitive tasks in healthy older adults and in people with early-diagnosed PD. Thus, we aim to uncover an early biomarker of movement (in)efficiency.

### Dissemination

The communication about the running, upcoming or past activities for the general and specific public are regularly uploaded to the webpage of the TwinBrain project (
www.twinbrain.si). In addition, the webpage and social media contain links to all media press, podcast series, and newsletters which are intended to reach a wide audience.

The scientific output of the study will primarily target researchers and medical doctors. The output of the proposed protocol will produce at least three scientific papers, which will be submitted to peer-review scientific journals. In addition, the results of the clinical trial will be disseminated at content-related conferences, seminars, and congresses, such as the International Congress of Parkinson’s Disease and Movement Disorders and the Mobile Brain/Body Imaging Conference.

The website will also be used for the long-term sustainability of the dissemination which will continue to communicate research findings and ongoing updates, and partnering with relevant organizations to continue research and dissemination efforts.

## Study status

The protocol has been tested on 5 pilot healthy young subjects, intended to detect potential issues with the software and recorded data. Upon resolving all the issues, three healthy older adults underwent the protocol to assess subjective fatiguing effects in the target age group and to identify the strategies to ameliorate the fatigue. Currently, 6 subjects had been tested, of which 4 belonged to the health group and 2 were participants with PD.

### Ethics and consent

The study will be conducted in accordance with the ethical standards of the 1964 Declaration of Helsinki and the guidelines of Good Clinical Practice. IRB of Trieste University Hospital – ASUGI, Trieste, Italy approved this study protocol (ASUGI protocol number: 106/2021). The study was registered on ClinicalTrials.Gov under code: NCT05477654. The informed consent for each study participant will be obtained by a medical doctor (MC or PM), a movement disorder specialist, employed by the Neurological Clinic Trieste. All participant information and data will be stored securely and identified by a coded ID number only to maintain participants’ confidentiality.

## Data Availability

No underlying data are associated with this article. Zenodo: Demographic and General Health Questionnaire.
https://doi.org/10.5281/zenodo.7768228
^
80
^ Data are available under the terms of the
Creative Commons Attribution 4.0 International license (CC-BY 4.0).
